### Sample size calculation

The sample size was calculated based on χ2 test. We considered a reduction of 40% in injury prevalence as clinically relevant. For this 40% reduction in period prevalence from 0.36 to 0.22, α of 0.05 and β of 0.80, adjusting for cluster correlations (estimated intraclass correlation of 0.05) and 11 participants per cluster, a sample of 21,17 clusters is needed [16]. Correcting for an estimated dropout rate of 30%, the sample size was set at 28 clusters (**total n = 308 approximately 2 groups of 154)**. The definition of a cluster is equal to one golf club.

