**Methods and design:**

The GRIPP study is a two-armed randomized controlled trial. Twenty-eight golf clubs with 11 golfers per club will be randomly allocated to the intervention or control group. The intervention group will perform the GRIPP intervention program, and the control group will perform their warm-up as usual. The GRIPP intervention is conducted with the Knowledge Transfer Scheme framework, which is a systematic process to develop an intervention. The intervention consists of 6 exercises with a maximum total of 10 min. The primary outcome is the overall prevalence (%) of golf injuries measured with the Oslo Sports Trauma Research Center (OSTRC-H) questions on health problems every fortnight. The secondary outcome measures will be exposure to golf and compliance to the intervention program.

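### The 21.17 clusters are the requirement per arm but were used as the trial total, so 28 clubs give about 50–60% power, not 80%

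*Protocol article*

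**What the plan says.** The section Sample size calculation of the protocol article states the test ("The sample size was calculated based on χ2 test"), the effect ("For this 40% reduction in period prevalence from 0.36 to 0.22"), the error rates ("α of 0.05 and β of 0.80") and the clustering assumption ("estimated intraclass correlation of 0.05"). From these it derives the requirement: "11 participants per cluster, a sample of 21,17 clusters is needed". It does not say whether this number is per arm or for the trial.

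The next step is "Correcting for an estimated dropout rate of 30%, the sample size was set at 28 clusters", and the bracket that follows fixes the trial: "total n = 308 approximately 2 groups of 154". The abstract confirms that 28 is the number for both arms together: "Twenty-eight golf clubs with 11 golfers per club will be randomly allocated to the intervention or control group".

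**The concern.** Formulas for comparing two proportions usually return the number per group. If the 21.17 clusters came from such a formula, the count has to be doubled before it becomes a trial total, and the text shows no doubling. The trial would then have half the clubs its own calculation requires.

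The Discussion presents this as, to the authors' knowledge, the first randomized trial of an injury prevention warm-up in golf. A reader who believes power was 80% may give a non-significant result more weight against the programme than it can bear.

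**Working it through.** **Inputs**, all from Sample size calculation: control proportion p1 = 0.36; 40% relative reduction, so p2 = 0.60 × 0.36 = 0.216 (printed rounded, as 0.22); alpha 0.05; power 0.80; intraclass correlation 0.05; 11 golfers per club; dropout 30%. Assumed: two-sided alpha, equal allocation, equal club sizes, and that 0.80 is the power although the text calls it β.

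**Reproducing the printed figure**

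- Mean proportion: (0.36 + 0.216)/2 = 0.288. Difference: 0.144.
- Golfers per arm without clustering: (1.96 + 0.8416)² × 2 × 0.288 × 0.712 / 0.144² = 7.849 × 0.4101 / 0.02074 = 155.23.
- Design effect: 1 + (11 − 1) × 0.05 = 1.5.
- Golfers per arm with clustering: 155.23 × 1.5 = 232.85.
- Clusters per arm: 232.85 / 11 = **21.17**, the printed value.
- Protocol's dropout step: 21.17 × 1.3 = 27.5, rounded up to 28.

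So 21.17, and the 28 that follows from it, are both per-arm numbers.

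**Could 21.17 be a total under another formula?** Clusters needed, with the design effect applied, over pooled, unpooled, mean-proportion, arcsine and continuity-corrected formulas:

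| Setting | Per arm | Total |
|---|---|---|
| Two-sided, p2 = 0.22 | 21.95–24.23 | 43.9–48.5 |
| Two-sided, p2 = 0.216 | 20.63–22.86 | 41.3–45.7 |
| One-sided, p2 = 0.22 | 17.29–19.47 | 34.6–38.9 |
| One-sided, p2 = 0.216 | 16.25–18.38 | 32.5–36.8 |

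No variant gives a total near 21.17.

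**Correct totals on the protocol's inputs**

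- Before dropout: 2 × 21.17 = 42.3 clusters (about 466 golfers); in whole clubs, 22 per arm, 44 clubs, 484 golfers.
- With the protocol's ×1.3 step: 28 per arm, 56 clubs, 616 golfers.
- With division by 0.70, which is what retaining the required number after 30% loss needs: 21.17/0.70 = 30.24, so 31 per arm, 62 clubs, 682 golfers.

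**Power of 28 clubs (14 per arm), 0.36 versus 0.22, two-sided 0.05**

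Effective n per arm = clubs × golfers per club / design effect. Power = Φ{[0.14√n − 1.96√(2 × 0.29 × 0.71)] / √(0.36 × 0.64 + 0.22 × 0.78)}.

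- No dropout: n = 14 × 11/1.5 = 102.7. Power = Φ[(1.4186 − 1.2577)/0.6340] = Φ(0.25) = **60%**.
- 30% of golfers lost (7.7 per club, design effect 1 + 6.7 × 0.05 = 1.335): n = 14 × 7.7/1.335 = 80.7. Power = Φ(0.00) = **50%**.
- With a t reference on 26 degrees of freedom: 58% and 48%.
- With p2 = 0.216: 63% and 52%.
- If 30% of clubs are lost instead of 30% of golfers within clubs: 46% (48% at p2 = 0.216).

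Solving the same power formula for p2 at 80% power gives 0.187 without dropout (a 48% reduction) and 0.167 with 30% dropout (a 54% reduction).

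**A check without the cluster formula.** The calculation needs 155 golfers per arm even with no clustering and no dropout. The trial enrols 154 per arm. It therefore reaches about 80% power (80.0% at p2 = 0.216, 77.5% at 0.22) only if the intraclass correlation is zero and nobody is lost, and the protocol assumes neither.

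**The case against.** Four points can be made for the protocol.

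- **The match needs 0.216, not the printed 0.22.** This is true, and it also needs one particular variance formula. That 21.17 is per arm is an inference, since the text leaves it unlabelled and the source it cites is not at hand. But 0.216 is what the stated 40% reduction gives, and with 0.22 the per-arm requirement is larger still.
- **Alpha may have been one-sided.** The text does not say. One-sided testing would not reproduce 21.17, and 28 clubs would still give only 72–74% power without dropout and 63–65% with 30% of golfers lost.
- **The planned analysis is a generalized linear mixed model, with injuries recorded every fortnight.** Repeated measurements might change the actual power. This stands as a limit on the figures above: they describe power under the protocol's own χ² calculation on one period prevalence. The calculation takes no credit for repeated measurements, and the document gives no within-person correlation from which to work out a gain, so this does not support the 80%.
- **The consequence can be overstated.** Without dropout, a true 40% reduction would be found in about 60–63% of such trials. The even chance applies only if the full 30% dropout occurs. How readers would take a null result is a prediction.

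None of these makes 28 clubs sufficient for the stated target.

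**Conclusion.** The error is real. A per-arm cluster requirement was carried forward as the trial total, so the trial has 28 clubs where the same inputs and the same dropout step call for 56. Power for the stated effect is about 60% without dropout and about 50% with 30% dropout (63% and 52% at the unrounded 0.216), in place of 80%.

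This rests on two-sided alpha, equal allocation, equal club sizes and the χ² basis that the protocol states. Unequal club sizes would normally lower the power further.

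Two smaller slips sit in the same section. The value 0.80 is labelled β, which read literally means 20% power. The dropout correction multiplies by 1.3 instead of dividing by 0.70; even if 21.17 had been a total, division would have given 30.2, so 31 clusters. Neither is needed for the main conclusion.

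**What to change.** Correct Sample size calculation as follows:

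1. State that 21.17 clusters are needed per arm, so 42.3 in total before dropout (44 whole clubs), and give the dropout-adjusted total: 56 clubs with the ×1.3 step, or 62 with division by 0.70.
2. State that the planned 28 clubs and 308 golfers give, on the protocol's own assumptions and for 0.36 versus 0.22, about 60% power without dropout and about 50% with 30% dropout. Add that the reduction detectable with 80% power is about 48% to 54%.
3. Write power of 0.80 in place of β of 0.80, and say that alpha is two-sided if that is so.
4. Preferably add that a non-significant result will be read from the confidence interval and not as absence of effect. This is advisable but not part of the arithmetic correction.

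The registration was retrospective (28 October 2021) and the intervention is set in the 2021 season, so the trial appears to have been under way already. The remedy proposed is therefore accurate disclosure, not a larger sample. The cost is protocol or SAP wording and a less favourable power statement; no extra participants are needed.

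### The step from 21.17 to 28 clusters does not cover a 30% loss of clubs; the level of dropout is unstated and the correction must be redone on the per-arm base

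*Protocol article*

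**What the plan says.** Everything needed is in the protocol article, under Sample size calculation.

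- Method and error rates: "The sample size was calculated based on χ2 test", with "α of 0.05 and β of 0.80". The 0.80 is evidently power.
- Effect: "For this 40% reduction in period prevalence from 0.36 to 0.22".
- Clustering: "estimated intraclass correlation of 0.05" and "11 participants per cluster".
- Result before dropout: "a sample of 21,17 clusters is needed".
- Result after dropout: "Correcting for an estimated dropout rate of 30%, the sample size was set at 28 clusters", which is "total n = 308 approximately 2 groups of 154".

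The abstract confirms that 28 is the number of clubs over both arms. The article prints no formula for the dropout step and does not say whether the 30% refers to clubs or to golfers.

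**The concern.** To have a required number left after losing a fraction d, one divides by 1 − d. Multiplying by 1 + d gives a smaller number, which falls short when the full loss occurs. The printed 28 fits the multiplication and not the division.

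The dropout allowance is the article's only stated protection of its power against attrition. If it is too small, or rests on an unstated idea of who drops out, the reader cannot tell what power remains. The input, the rate and the result are all printed, so this is a question of whether they agree, not of detail left to a fuller document.

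**Working it through.** **Inputs** (Sample size calculation): control prevalence 0.36; 40% reduction, printed as 0.22 (unrounded 0.36 × 0.6 = 0.216); α 0.05, taken as two-sided because sidedness is not stated; power 0.80; intraclass correlation 0.05; 11 golfers per club; dropout 30%.

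**1. Reproducing the dropout step.**
- Multiplication: 21.17 × 1.3 = 27.52, rounded up to 28. This is the stated figure.
- Division: 21.17 / 0.7 = 30.24, rounded up to 31 (32 for equal arms). This is not the stated figure.

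**2. If whole clubs are lost.** 28 × 0.7 = 19.6 clubs remain, against 21.17 required. On that base the tolerated loss is 1 − 21.17/28 = 24.4%. The raw golfer counts (308 × 0.7 = 215.6 against 21.17 × 11 = 232.9) can be compared only in this case, because the design effect then stays at 1 + 10 × 0.05 = 1.5.

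**3. If golfers are lost evenly within clubs.** Mean club size is 11 × 0.7 = 7.7 and the design effect is 1 + 6.7 × 0.05 = 1.335.
- Effective sample required by the base: 21.17 × 11 / 1.5 = 155.2.
- Effective sample from 28 clubs: 28 × 7.7 / 1.335 = 161.5, which exceeds 155.2.
- Clubs needed: 155.2 × 1.335 / 7.7 = 26.9.

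On the protocol's base figure, the lower design effect therefore removes the whole shortfall.

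**4. What 21.17 is.** The two-proportion formula is n per arm = (z0.975 + z0.80)² × 2p̄(1 − p̄) / d². With p2 = 0.216, p̄ = 0.288 and d = 0.144:
- n per arm = 7.849 × 2 × 0.288 × 0.712 / 0.144² = 155.2
- with the design effect: 155.2 × 1.5 = 232.9 golfers per arm
- 232.9 / 11 = 21.17 clubs **per arm**

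Pooled, unpooled and arcsine formulas were also tried, one- and two-sided, with and without continuity correction, at p2 = 0.22, 0.216 and 0.21. None gives 21.17 as a total at design effect 1.5; the totals run from 29.7 to 48.8 clubs.

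**5. Power of 28 clubs in total.** With n the effective number per arm, power = Φ{[d√n − 1.96√(2p̄(1 − p̄))] / √(p1(1 − p1) + p2(1 − p2))}.

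| Case | Effective n per arm | Power, p2 = 0.22 | Power, p2 = 0.216 |
|---|---|---|---|
| No dropout | 28 × 11 / 1.5 / 2 = 102.7 | 60% | 63% |
| 30% of clubs lost | 19.6 × 11 / 1.5 / 2 = 71.9 | 46% | 48% |
| 30% of golfers lost within clubs | 28 × 7.7 / 1.335 / 2 = 80.7 | 50% | 52% |

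**6. Dropout on the per-arm base** (2 × 21.17 = 42.34 clubs in total).
- Loss of clubs: 42.34 / 0.7 = 60.5, so 62 for equal arms (31 per arm, 682 golfers). Repeating × 1.3 would give 55.04, so 56.
- Loss of golfers within clubs: 2 × 26.9 = 53.8, so 54 (27 per arm, 594 golfers).

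**The case against.** The strongest reply is that the 30% is loss of golfers. Each golfer consents individually and fills in a form every fortnight, and the programme is individual and unsupervised. On that reading 28 clubs suffice on the protocol's base figure and tolerate about 33.7% golfer loss (mean 7.29 per club). This stands. A reader might infer from the arithmetic that 28 clubs cannot cover 30% dropout at all. The article does not support that, because it never says that clubs are what is lost.

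Three limits apply to the reply. The article does not make the argument: it inflates the number of clubs and keeps 11 in each (28 × 11 = 308). The margin is thin: if the same loss of golfers includes four whole clubs, 24 clubs of 8.98 remain, with design effect 1.399 and effective size 154.1, just below 155.2. And the cover exists only if 21.17 is a total for both arms, which it does not reproduce as.

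It can also be said that the multiplication is inferred. That is so, but the result for loss of clubs does not depend on it: 28 × 0.7 is below 21.17 however 28 was reached.

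**Conclusion.** The printed figures do not support 30% dropout if it means loss of clubs. They do support it, on the protocol's own base, if it means even loss of golfers within clubs. The article leaves this open, so its statement that 30% is allowed for cannot be relied on as written. Taken alone, the dropout step is worth between zero and three clubs (31 against 28).

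The low power should not be blamed mainly on this step. Using a per-arm figure as the total already brings power to about 60–63% before any dropout. Dropout then lowers it to 46–48% (clubs) or 50–52% (golfers). Raising 28 to 31 alone would leave it at about 49–57% after dropout. These figures assume a two-sided test, 1:1 allocation (consistent with blocks of 2 and 4), the stated intraclass correlation and, for golfer loss, even loss across clubs.

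**What to change.** In Sample size calculation:

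1. State whether the 30% is loss of clubs or of golfers within clubs.
2. Apply the matching correction: divide by 0.7 for clubs, or recompute at 7.7 golfers per club with design effect 1.335.
3. Apply it to the per-arm base of 21.17. This gives 62 clubs in total for club loss or 54 for golfer loss, with equal arms.
4. If the trial stays at 28 clubs, report the power after 30% dropout: about 46–48% or 50–52%, according to the level of loss, in place of 80%.

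Do not substitute a sentence saying that 28 clusters cover 24% loss. It would take 21.17 as the total for both arms and so print a second wrong figure.

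If the number of clubs is fixed, the cost is wording and a less favourable stated power. No change to design or conduct is needed to correct the text.

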### Statistical analyses

Data analysis will be performed using the Statistical Package for the Social Sciences (SPSSS). Descriptive statistics will be performed for golfers’ baseline characteristics and golf injuries of the past 12 months. For the primary outcome, a generalized linear mixed model will be used to examine the effect of the GRIPP intervention on injury prevention. The randomization location (intervention or control group) will be an independent variable. The occurrence of injury will be used as a dependent variable. Possible confounders will be analysed in the model.

## Discussion

To the best of our knowledge, there have been no previous randomized trials testing an injury prevention warm-up protocol for golfers. The GRIPP study will compare the conducted warm-up protocol with a control group who perform their warm-up as usual. Golfers of all levels are likely to benefit from the conducted warm-up protocol compared with the positive results of other effective warming-up prevention programs [16–18]. The developed program is an individual unsupervised golf athlete intervention and reflects the daily practice of predominantly unsupervised exposure of amateur golfers.

It is uncommon in an individual intervention prevention program study to cluster randomize. We developed an unsupervised program and our program reflects the daily practice. However, these unsupervised programs have problems with adherence and compliance rates [30, 32]. For example, an unsupervised intervention study advised future studies in tennis for potential improvement of adherence and exercise quality to test in a coach-based setting [30]. Based on the knowledge obtained during the development process and the reflection of daily practice, it was suggested to randomise per club, so golfers are informed and able to speak freely and practice with this warm-up. We will monitor this problem and further unsupervised exercise programs in individual sports might have advantage of our experiences of our randomization strategy.

We need to be conscious that there might be other reasons for the occurrence of injuries, such as golf professional influence and a suboptimal technique. However, it is difficult to identify this. There are presumptions that swing faults might influence the occurrence of specific golf injuries. The golfers in our study are amateur golfers of 45 years and older. These golfers likely have their own personal body limitations and injury history, and therefore each golfer has its own unique swing based on these limitations. The influence of a suboptimal swing is out of the scope of this study. It is plausible that golfers at this age and amateur level all have swing faults.

## Data Availability

Not applicable.

## Abbreviations

GRIPP: Golf Related Injury Prevention Program
GRI’s: Golf-related injuries
KTS: Knowledge Transfer Scheme
OSTRC-H: Oslo Sports Trauma Research Center questions on health problems
RCT: Randomized controlled trial
WMO: Medical Research Involving Human Subjects Act
